## PURPOSE AND OBJECTIVES

**Purpose:** *The importance of the research and the potential knowledge to be gained should be explained in detail. Give background information.*

Smoking during pregnancy is the leading preventable cause of poor pregnancy outcomes in the U.S. and other developed countries, increasing risk for pregnancy complications, preterm birth, stillbirth, infant death, impaired lung development, childhood illness and developmental/behavioral problems, and lifelong increased risk for cardiovascular disease, obesity, and metabolic syndrome. Prevalence of smoking during pregnancy among national samples of U.S. pregnant women has remained stagnant at approximately 13% over the past decade. Because risk for maternal smoking during pregnancy is disproportionately high among economically disadvantaged women, it contributes substantially to the problem of health disparities.

Existing treatments for smoking cessation among pregnant smokers produce very low quit rates ( $< 15\%$ ) with the exception of financial incentives. Meta-analyses indicate that incentive-based treatments produce the largest effect sizes of any psychosocial or pharmacological intervention for promoting smoking cessation during pregnancy. Additionally, two randomized, controlled trials conducted by our research group demonstrated that incentives significantly increase sonographically estimated fetal growth, increasing abdominal circumference (cm/week), femur length (cm/week), and overall estimated fetal weight compared to control groups that received non-contingent incentives. Retrospective analyses of birth outcome data aggregated across three previous trials from our group also indicated that incentives significantly increased mean birth weight, decreased the percent of low birth weight deliveries ( $< 2500$  g), increased the percent of women breastfeeding through 12-weeks postpartum, and decreased depressive symptoms from birth through 12-weeks postpartum among depression-prone women. Although this evidence-based treatment has demonstrable capacity to reduce smoking and improve birth outcomes, the scalability of this approach is constrained by the frequent clinic visits necessary for

biochemical verification of smoking status, which limits access to those in the immediate vicinity of clinics that can provide such care. ***Capitalizing on technological advancements may surmount such access barriers, with the potential to extend the reach of financial incentives to disadvantaged pregnant smokers nationwide.***

**The overarching aim of the current study is to develop an innovative, efficacious, remotely delivered financial incentives intervention to reduce cigarette smoking during pregnancy.** To enable flexible use of the intervention in diverse locations, we will use a mobile-phone-based platform for delivering the incentives intervention. Recent data indicate that over 80% of pregnant women drawn from a U.S. nationally representative sample own a smartphone. The platform will involve a Smartphone “app” which uses video capture to verify smoking status via a breath carbon monoxide (CO) monitor along with saliva cotinine test kits, and ensures treatment fidelity by providing automated, immediate feedback, incentive calculations, and incentive delivery for abstinence. Comparable technology-based treatment delivery platforms have been used to successfully promote smoking abstinence among the general population of U.S. smokers and among other vulnerable populations including rural heavy smokers.

The proposed study addresses the following specific aims:

**Aim 1:** Examine the feasibility, efficacy, and cost-effectiveness of a mobile-phone-based incentives intervention for promoting smoking cessation among economically disadvantaged (i.e., Medicaid insured) pregnant women. We will accomplish this aim by randomly assigning 152 pregnant women who are still smoking at their first prenatal care visit to receive incentives contingent on biochemically verified smoking abstinence or best practices for promoting smoking cessation. Incentives will be in place from the start of prenatal care through three months postpartum. Primary outcomes will be point prevalence smoking abstinence, continuous abstinence during and following pregnancy, and birth outcomes (mean birth weight, gestational age, NICU admissions). We hypothesize that there will be higher abstinence rates, longer durations of abstinence, and improved birth outcomes in the incentives versus the best practices condition.

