#### **Statistical Methods**

Study conditions will be compared on baseline demographics and other characteristics using analysis of variance (ANOVA) for continuous variables and chi-square tests for categorical variables. If a specific characteristic differs significantly across study conditions and is predictive of the outcome, it will be considered as a potential covariate in subsequent analyses. Analyses of treatment effects on smoking status will adhere to an intent-to-treat approach whereby all women randomized to each study condition will be included in the analyses independent of early dropout, noncompliance, etc., with the exception of women excluded for abortion/fetal demise as is convention in this research area. Cochran-Mantel-Haenszel tests (C-M-H) will be performed for comparisons between the incentives vs. usual care conditions on point-prevalence smoking abstinence at end-of-pregnancy and 6-months postpartum assessments with referring clinic as a stratification variable. The Breslow-Day Test will be used to examine the homogeneity of treatment effects across referring clinics. Comparisons of point-prevalence abstinence rates between treatment conditions across all assessments through six months postpartum will be analyzed using mixed model repeated measures for categorical data based on generalized estimating equations (GEE) using a logistic link function (SAS: PROC GENMOD, SAS Institute, Cary, NC). The two treatment groups will also be compared on birth outcomes, breastfeeding, and other measures collected postpartum. Comparisons of treatment conditions on dichotomous outcomes (e.g., % low birth weight, % preterm, % NICU admissions, % breastfeeding) will parallel categorical analyses for point prevalence abstinence using PROC GENMOD to adjust for strata (referring clinics) and potential covariate effects. Analysis of covariance (ANCOVA) will be used to compare study conditions on mean birth weight adjusting for variables known to influence birth weight (% maternal pre-pregnancy BMI, parity, and sex) and mean gestational age at delivery. The significance criterion will be set at  $\alpha = 0.05$  for all analyses.

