#### Sample Size Justification

Based on data from (a) our prior and ongoing trials which utilized a comparable schedule of routine smoking monitoring visits and schedule of potential earnings, and (b) previous trial data indicating a 20% decrease in abstinence rates from late pregnancy to 24-weeks postpartum, we expect late-pregnancy abstinence rates of approximately 40% vs. < 10% (incentives vs. best practices, respectively), and 24-week postpartum abstinence rates of approximately 20% vs. < 5%. The proposed sample size of 76 per treatment condition will result in at least 80% power to detect a difference between the two treatment conditions in abstinence rates of 40% vs. 10 % at late-pregnancy or 20% vs. 5% at 24-weeks postpartum assessments using a chi-square test. This proposed sample size is also expected to be more than sufficient for examining differences between treatment conditions in birth weight and breastfeeding outcomes. With respect to mean birth weight, power is estimated to be 60% to detect a difference of approximately 200 g between the incentives versus best practices conditions assuming a pooled standard deviation (SD) of 550 g, which aligns well with treatment effects in our study aggregating birth outcomes across our first three controlled trials whereby mean birth weights were  $3295.6 \pm 588$  g vs.  $3093.6 \pm 404$  g in the incentives versus control conditions, respectively. We are estimating breastfeeding rates of 50% and 30% in the incentives condition and 17% and 13% in the best practices condition at 12 and 24-weeks postpartum based on our prior study results. Using chi-square tests, we will have over 75% power to detect differences in breastfeeding rates between the incentives versus best practices conditions at the two assessments. Power calculations were done using a two-sided significance level of 0.05. A sample size of 60 for the arm targeting AI/AN women was selected based on initial pilot studies of the financial-incentives-based approach to promoting smoking cessation among pregnant women developed at the University of Vermont (Higgins et al., 2004). This sample size will be sufficient to determine whether the intervention is feasible and effective at promoting late-pregnancy smoking abstinence between AI/AN women enrolled in the Incentives versus Best Practices Control conditions. Results of our assessment will be used to inform power analysis calculations for larger-scale, NIH-supported research proposals focused on smoking cessation among AI/AN pregnant women.

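### Five unranked primary outcomes, at least six comparisons each tested at 0.05, and no rule for which result decides efficacy

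*Protocol*

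**What the plan says.** Protocol, Purpose and Objectives, Aim 1: "Primary outcomes will be point prevalence smoking abstinence, continuous abstinence during and following pregnancy, and birth outcomes (mean birth weight, gestational age, NICU admissions". The sentence ranks none of the five. The Objectives paragraph adds no deciding outcome; its primary objective covers feasibility, efficacy and cost-effectiveness together.

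Protocol, Statistical Methods: Cochran-Mantel-Haenszel tests compare the arms on "point-prevalence smoking abstinence at end-of-pregnancy and 6-months postpartum assessments with referring clinic as a stratification variable". A further analysis, by GEE, covers "Comparisons of point-prevalence abstinence rates between treatment conditions across all assessments through six months postpartum". Birth weight and gestational age are compared by ANCOVA and NICU admission by a logistic model. No specific test is named for continuous abstinence. On the error rate: "The significance criterion will be set at" 0.05, and this is applied to every analysis. No order, adjustment or success rule follows.

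Protocol, Sample Size Justification: "The proposed sample size of 76 per treatment condition will result in at least 80% power" for 40% vs. 10% "at late-pregnancy or 20% vs. 5% at 24-weeks postpartum assessments using a chi-square test". For mean birth weight, "power is estimated to be 60% to detect a difference of approximately 200 g", with an SD of 550 g. No power is given for gestational age, NICU admissions or continuous abstinence. "Power calculations were done using a two-sided significance level of 0.05".

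**The concern.** A primary outcome is the result on which the efficacy claim stands or falls. Here five share that status and the protocol does not say how they combine. Two readings are open, and each causes trouble.

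- **Any one suffices.** The trial then has six or more chances at 0.05 to claim a primary success, and the error rate for the claim is well above the nominal level.
- **All must succeed.** Error is then not inflated, but the power of the whole cannot exceed that of its weakest member. That is at most 60%, because birth weight alone has only that.

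The sample-size text does not settle the matter, since it powers late pregnancy or 24 weeks without saying which decides. The protocol says the next, larger proposal depends on the intervention proving acceptable and efficacious, so the reader needs to know in advance which result would show efficacy. A significant NICU or gestational-age result beside null abstinence results could be reported as a primary success. Conversely, a clear effect on smoking could sit beside a failed primary outcome that the trial was never sized to show.

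**Working it through.** **Inputs.** From Sample Size Justification: 76 per arm, two-sided 0.05, 40% vs. 10% at late pregnancy, 20% vs. 5% at 24 weeks postpartum, 200 g difference in birth weight with SD 550 g. From Aim 1: five primary outcomes. From Statistical Methods: two time points for point prevalence. Correlations among the tests are not in the protocol and are assumed over a range.

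**1. The plan's own power.** Chi-square, pooled variance under the null, no continuity correction: power = Φ[(d − 1.96·SE0)/SE1].
- Late pregnancy: d = 0.30; SE0 = √(2·0.25·0.75/76) = 0.0702; SE1 = √((0.24 + 0.09)/76) = 0.0659; Φ(2.46) = 99.3%.
- 24 weeks: d = 0.15; SE0 = √(2·0.125·0.875/76) = 0.0537; SE1 = √((0.16 + 0.0475)/76) = 0.0523; Φ(0.86) = 80.5%.
- Birth weight: SE = 550·√(2/76) = 89.2 g; Φ(200/89.2 − 1.96) = Φ(0.28) = 61%.

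The stated figures of at least 80% and of 60% both reproduce.

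**2. Count of comparisons.** Five named outcomes, with point prevalence tested at two time points, give six. The all-visit GEE would make seven.

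**3. Chance of at least one false significant result, either direction, all nulls true, independent tests:** 1 − 0.95^k.

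| k | either direction | favouring incentives, 1 − 0.975^k | ceiling for the latter, 0.025k |
|---|---|---|---|
| 1 | 5% | 2.5% | 2.5% |
| 5 | 22.6% | 11.9% | 12.5% |
| 6 | 26.5% | 14.1% | 15% |
| 7 | 30.2% | 16.2% | 17.5% |

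The ceiling holds whatever the correlation.

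**4. Correlated tests, k = 6, either direction** (multivariate-normal simulation).
- Correlation only within the three smoking tests and within the three birth tests: 25.4% at 0.3, 23.4% at 0.5, 20.7% at 0.7.
- The same correlation among all six: 25.4% at 0.2, 22.5% at 0.4, 20.7% at 0.5, 18.6% at 0.6, 16.4% at 0.7. The figure drops below 20% at about 0.55.

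**5. Remedies compared at 76 per arm.**
- Fixed sequence, late pregnancy then 24 weeks, each at two-sided 0.05: familywise error for the two tests stays at 5%. Power is 99.3% for step 1. The chance of winning both is 0.993 × 0.805 = 79.9% if independent, and at least 0.993 + 0.805 − 1 = 79.8% under any dependence.
- Bonferroni over six (0.05/6 = 0.00833 each): 95.9% for late pregnancy, 56.4% for 24 weeks, about 34% for birth weight.
- Slack: with 68 per arm step 2 has 75.9%, and with 60 per arm 70.5%. Step 1 still has 97.5% at 60 per arm.

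**The case against.** Several points on the other side are sound.

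- **A false-success rate above 20%.** A reader might infer this from the 23% to 26%. The protocol does not support it: its tests are two-sided and its hypotheses directional, and those percentages include false results against incentives. A false result favouring incentives cannot exceed 15% with six tests or 17.5% with seven.
- **The count.** A reader might speak of six primary outcomes. Aim 1 names five; the sixth comparison is a second time point, and the test for continuous abstinence is implied rather than specified.
- **Independence.** Continuous abstinence overlaps with point prevalence by construction, and the three birth outcomes come from the same delivery. Independence is therefore an upper-end assumption, and strong correlation across all six takes the two-sided figure below 20%.
- **Unpowered birth outcomes.** This is too strong for birth weight, which is underpowered at a stated 60%. Gestational age and NICU admissions simply have no stated power.
- **Implicit emphasis.** The trial is sized on abstinence, birth weight comes in as a further benefit, and the work is meant as preliminary data. With 99.3% power at late pregnancy, the lead conclusion is unlikely to turn on multiplicity. All of that lowers the severity, but an emphasis is not a decision rule.
- **The SAP.** Multiplicity procedures are often left there. This protocol, however, is not silent: it fixes five primaries and 0.05 for every analysis, so a hierarchy in the SAP would contradict it.

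**Conclusion.** The concern holds and should be fixed. The protocol makes five outcomes primary without rank, tests them in at least six comparisons at 0.05 each, and gives no rule for deciding efficacy. If any one significant result is taken as success, which is an assumption because the protocol does not say, the chance of at least one false significant primary result in either direction is about 23% for five and 26% for six independent tests. It is about 21% to 25% for six tests with within-block correlations of 0.7 to 0.3, and below 20% if all six correlate at about 0.55 or more. The chance of a false result favouring incentives is about 14% for six independent tests, more than five times the 2.5% of a single test. On the plan's own figures there is also about a 40% chance of missing a true 200 g birth-weight effect, and three of the five primaries carry no power statement. The practical exposure is over-claiming on birth outcomes more than a wrong lead conclusion on smoking.

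**What to change.** Name biochemically verified point-prevalence abstinence at the late-pregnancy assessment as the single primary outcome, using the protocol's own definition of that assessment and the same label in Statistical Methods, which speaks of end of pregnancy. Do not import a 7-day window unless it is deliberately added: in this protocol seven days is a screening criterion, not the outcome definition. Test 24-week postpartum abstinence second, only if the first test is significant, both at two-sided 0.05. Make continuous abstinence, the all-visit GEE and the three birth outcomes secondary, reported with 95% confidence intervals and no confirmatory claim. Confine the flat 0.05 statement accordingly.

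Other orderings or an alpha split would also close the gap. This one fits the stated basis for the sample size and needs no more participants, whereas an even split over six tests would cut the 24-week power to 56.4%.

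Costs: birth outcomes lose primary status, which 60% power hardly supported. The 24-week step has no slack. Its 80.5% assumes an unstratified chi-square with all 76 per arm, while the plan stratifies by clinic and excludes women with abortion or fetal demise, at a rate it does not give. A protocol amendment is needed, and it should be made before anyone sees outcome data by arm.

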**METHODS AND PROCEDURES**

**Study Design:** Describe the research design, including a description of any new methodology and its advantage over existing methodologies.

We are proposing a two condition, parallel groups, randomized controlled trial (RCT) of a mobile-phone-based financial incentives intervention targeting economically disadvantaged pregnant cigarette smokers. The experimental group will receive electronic vouchers contingent on the remote submission of breath carbon monoxide (CO) samples indicating smoking abstinence whereas the control group will receive best practices for promoting smoking cessation. The use of a best practices control group reflects a real-world comparison condition in that all women will receive the treatment that practitioners in the community are instructed to provide (i.e., the 5As plus quit-line referral) thereby enhancing the ecological validity of the study, while also minimizing between-subject variability in the extent of participants' exposure to these practices by implementing these treatment components ourselves (described in greater detail below). Although one common alternative is to use a non-contingent incentives control group which equates both groups in terms of overall earnings, a meta-analysis conducted by our group showed that non-contingent incentives have no impact on abstinence levels above no-incentive control conditions. Alongside the two condition, parallel groups RCT described above, we will recruit an additional 60 American Indian/Alaska Native (AI/AN) women at another site (Alaska Native Tribal Health Consortium, Anchorage, Alaska) to examine effects of the present mobile-phone-based incentives intervention among this specific subgroup of women. Although this smaller subset of women will be randomized separately within an arm that is separate from the main trial, all study protocols and procedures will be identical in the AI/AN arm relative to the main trial. The rationale for a separate arm targeting AI/AN women is that smoking prevalence is substantially higher among this subpopulation (i.e., ~ 36% for AN women (Patten et al. 2018) versus ~ 13% among U.S. pregnant women overall (Kurti et al., 2017), they exhibit unique tobacco use characteristics including use of a homemade smokeless tobacco (Iqmik, Hurt et al., 2009), and very few smoking cessation interventions have been implemented specifically among AI/AN women (Patten et al., 2010; Patten et al., 2018). Thus, the present smartphone-based incentives intervention—which has never been implemented previously among this subpopulation—will be examined among a subset of 60 AI/AN women. AI/AN women will be recruited at a separate site (ANTHC, Anchorage, AK), and separate IRB approvals will be obtained as mandated by the collaborating location.

**Procedures:** Describe all procedures (sequentially) to which human participants will be subjected. Identify all procedures that are considered experimental and/or procedures performed exclusively for research purposes. Describe the types, frequency and duration of tests, study visits, interviews, questionnaires, etc. Include required screening procedures performed before enrollment and while on study. Please provide in table, list or outline format for ease of review. (describe and attach all instruments)

Note: A clinical research protocol may involve interventions that are strictly experimental or it may involve some aspect of research (e.g., randomization among standard treatments for collection and analysis of routine clinical data for research purposes). It is important for this section to distinguish between interventions that are experimental and/or carried out for research purposes versus those procedures that are considered standard therapy. In addition, routine procedures performed solely for research purposes (e.g., additional diagnostic/follow-up tests) should be identified.

**Participants** Study participants will be 152 pregnant Medicaid recipients  $\geq 18$  years of age and their infants (304 subjects total). Mom's will be recruited from obstetric practices and WIC offices located in all Vermont counties, and from obstetric practices and WIC offices outside Vermont. We will use the same procedures to recruit as our prior and ongoing trial, as well as the print and online advertising strategies (e.g., local newspapers, Facebook, Craigslist) that were developed for use in our current trial. An additional, smaller subset of 60 pregnant AI/AN women will be recruited using a combination of these two methods in Alaska. Briefly, pregnant women attending their first prenatal care visit will be identified from the obstetric clinic's appointment schedules. Receptionists at each practice will request that these women complete a brief self-administered smoking-screening form containing a multiple-choice question on smoking status that has been validated to enhance accurate reporting. These forms will be returned via fax to the Substance Abuse Treatment Center ([name]). Only those identified as key personnel on the proposed study have access to the fax machine in the SATC. Women who endorse smoking in the 7 days prior to completing the screening form and provide contact information will be contacted by research staff to further verify study eligibility and provide additional information about the study. Regarding our print and online advertising strategies, participants will self-refer after seeing our ads and will complete a screening online or over the telephone with research staff. Prior to enrolling in the study, women who self-refer will be asked to sign a medical release form allowing us to contact their healthcare provider or local WIC director to verify their current pregnancy status.

For inclusion in the study, women must meet the following criteria: (a)  $\geq 18$  years of age, (b) report being smokers at the time they learned of the current pregnancy, (c) report smoking in the 7 days prior to completing their preliminary eligibility screening, (c)  $\leq 25$  weeks pregnant, (d) speak English, (e) own a smartphone (Android or iOS; 81.8% of pregnant women in wave 1 [2013-2014] of the Population Assessment of Tobacco and Health

[PATH] reported owning a smartphone). Exclusion criteria include: (a) current or prior mental or medical condition that may interfere with study participation (assessed via self-report during formal intake assessment completed online or by phone using a medical and psychosocial history questionnaire), (b) smoke marijuana more than once each week and not willing to quit (marijuana smoking can inflate breath CO), (c) exposed to unavoidable occupational sources of CO (e.g., car mechanic), (d) report currently receiving opioid maintenance therapy (e.g., methadone, buprenorphine). Women who meet the inclusion criteria and complete the informed consent process will be considered formally enrolled and will be mailed equipment to participate in the study, but will not be randomized until they (1) confirm receipt of their equipment, (2) complete an orientation session on the smartphone app used in the current study (described subsequently), and (3) provide a saliva sample indicating current smoking (i.e., test strip returns a positive for cotinine, a metabolite of nicotine). Upon completing these steps, women will be randomized to either the incentives or best practices treatment condition (See Treatment Conditions). The only criteria for withdrawing participants after randomization occurs will be pregnancy termination or fetal demise.

